## Abstract

**Methods/design::**

In this prospective cohort study, we plan to enroll 430 participants including 215 CAPS patients and 215 healthy controls. The CAPS group takes duloxetine 30 mg per day as an initial dose. Patients will have 24-week medication period and follow up at week 0, 4, 12, 24 and 36. Blood samples will be obtained from patients at every visits and health controls at the initial visit and a series of questionnaires will be completed by the participants. The primary end points are: The differential expression of miRNAs between CAPS groups and healthy control groups at baseline. The changes in abdominal pain scores before and after duloxetine treatment in patients with CAPS and their relationship with the changes in miRNAs. The secondary end point is the changes in scores of depression, anxiety, sleep quality and quality of life before and after duloxetine treatment in patients with CAPS and their relationship with changes in miRNAs.

**Discussion::**

Findings of study will provide the reliable basis for diagnosis and the predictor of duloxetine efficacy of CAPS. Importantly, findings grant patients a chance to benefit from treatment.

## 1. Introduction

According to Rome IV criteria, centrally mediated abdominal pain syndrome (CAPS) is characterized by continuous, nearly continuous, or frequently recurrent abdominal pain that is often severe and only rarely related to gut function. CAPS is associated with loss of function across several life domains, including work, intimacy, social/leisure and must be present for at least 6 months before diagnosis.^[1]^

The prevalence of CAPS ranges from 0.5% to 2.1% which is lower than other functional gastrointestinal diseases, such as irritable bowel syndrome (IBS) and functional dyspepsia.^[2]^ However, it is worth note that CAPS has a relatively serious impact on daily life among functional gastrointestinal diseases. Chronic and recurrent pain was the main reason why people visits to gastroenterology outpatient clinic repeatedly.^[3]^ Most of them take numerous unnecessary examinations, receive negative results. Heavy socioeconomic costs include utilization of medical resources and unemployment due to illness.^[4]^ However, the diagnosis of CAPS remains difficult. At present, based on ROME IV criteria, diagnosis of CAPS mainly depends on symptoms, duration and which is an exclusionary diagnosis. It is essential to find a specific and sensitive biomarkers to make a precise and rapid CAPS diagnosis.

Previous studies demonstrated that CAPS resulted from central sensitization with disinhibition of pain signals rather than increased peripheral afferent excitability.^[5]^ Psychological factors will influence human pain perception and down-regulate pain inhibition. Published literacy demonstrated that antidepressants and psychological therapy were potential therapy approaches. Duloxetine is a new SNRIs, mainly inhibits the serotonin and norepinephrine reuptake simultaneously.^[6]^ Current evidence demonstrated that Duloxetine can improve CAPS patients’ frequency of abdominal pain and anxiety.^[7]^ A cohort study of 103 patients found that 53% of patients (n = 10/19, *P* = .007) responded using 1 centrally acting neuromodulator, and effectiveness of duloxetine in CAPS group was 71%.^[8]^ Despite duloxetine seemed to be the most potent single agent neuromodulator, a clutch of patients get unsatisfactory effect. Unfortunately, there is currently a lack of means to predict therapeutic efficacy of duloxetine.

In the field of pain, current study has focused on 2 mechanisms, DNA methylation and miRNA expression.^[9]^ Micro RNAs are a class of a small noncoding RNAs that capable of silencing and post-transcriptional regulation of gene expression. Researchers have found grater variability of miRNA expression between IBS patients and healthy control, such as miR-199a-5p, miR-199b-5p, miR-29a3p, miR-219a-5p, miR-338-3p.^[10]^ Helena Kyunghee Kim et al found that miR-16-5p, hsa-miR-146a-5p and hsa-miR-21-5p were a potential predictive biomarkers of duloxetine response in patients with depression.^[11]^ In our pilot study, we also found differential expression profiles of serum miRNAs between CAPS patients and healthy controls. We therefore hypothesized that these miRNAs could be a potential biomarkers to diagnosis CAPS and predict efficacy of duloxetine.

To date, there is little information available regarding miRNA expression profile in serum of CAPS and predictor of duloxetine efficacy. Thus our study aims to explore the specific miRNAs in serum to solve this problem.

We present the protocol in accordance with the SPIRIT reporting checklist.

## 2. Methods and analysis

### 2.1. Study design

This study is a prospective cohort study conducted in China (ChiCTR2200064371). Our study aims to explore serum miRNAs as a diagnostic biomarker and a predictor of efficacy of duloxetine for patients with CAPS.

Blood samples will be taken from participants who visited our hospital. A total of 215 CAPS patients and 215 healthy controls will be enrolled from the inpatient and outpatient departments of gastroenterology and the digestive endoscopy center respectively.

### 2.2. Study hypothesis

We hypothesized that: there is differential expression of miRNAs between CAPS group and healthy control group; duloxetine would improve abdominal pain; and miRNAs may be associated with the prognosis of patients with CAPS after duloxetine treatment.

### 2.3. Study purpose

To evaluate the differential expression of miRNAs in patients with CAPS and healthy controls, to provide new biomarkers for diagnosis of CAPS.To explore the association between the changes of miRNAs and the efficacy of duloxetine treatment at week 4, 12, 24 and 36 in patients with CAPS.

### 2.4. Studying settings and recruitment

This study is now conducted at Ruijin Hospital from October 1, 2022 to December 31, 2023. We decide to recruit CAPS patients from the inpatient and outpatient of departments of gastroenterology. Meanwhile, the healthy controls will be recruited from the individuals who visit the digestive endoscopy center for routine checkups of gastroscopy and colonoscopy. All participants who experienced physicians will be screened for enrollment eligibility. Diseases will also be diagnosed by experienced gastroenterologists. To enhance participants compliance, they will make appointment for next visit when outpatient clinical visits and will be reminded via telephone or message.

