### 2.5. Eligibility criteria

#### 2.5.1. Inclusion criteria.

All CAPS patients must meet all of the following criteria: age at 18 to 85; meet the Rome IV diagnostic criteria; a signed and dated informed consent form; and commit to comply with study process and align with implementing the whole study process

All healthy controls must meet all of the following criteria: age at 18 to 85; no abdominal pain and other gastrointestinal symptoms; no organic lesions at gastroenterological endoscopy in latest 6 months; a signed and dated informed consent form; and commit to comply with study process and align with implementing the whole study process.

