### 2.7. Study procedure and timeline

The study procedure and timeline is illustrated as Figure 2 and Table 1. Heart rate, blood pressure, weight will be recorded at every visits. At the initial visit (visit1), patients will be diagnosed with CAPS by an experienced gastroenterologist. Patients and healthy controls will be screened by a experienced gastroenterologist. All of them will sign an informed consent form. Demographic and baseline data will be collected. The subjects will be asked to complete a series of questionnaires in order to get baseline scores. Baseline scores on the Numerical Rating Scale, the HAMA, Generalized Anxiety Disorder7, Hamilton Depression Scale, Patient Health Questionaires 9, Short Form 36, Pittsburgh sleep quality index will be obtained. Blood routine, biochemical indicators and genotype will also be carried out in the laboratory of Ruijin Hospital. On the ground of experimental method of Real-Time Fluorescence Quantitative PCR, the serum miRNAs will be sequenced between patients with CAPS and healthy control group.

**Table 1 T1:** Study timeline.

Visits	Screening period	Treatment period		Therapy termination	Follow-up period
	1	2	3	4	5 (Follow-up 1)
Treatment period (mo)	0	1	3	6	9
Informed consent form	x				
Demography and baseline	x				
Inclusion/exclusion	x				
NRS	x	x	x	x	x
HAMA/HAMD/PSQI/GAD7/PHQ9/SF36	x	x	x	x	x
PRS		x	x	x	x
QoL	x	x	x	x	x
Morisky questionnaire		x	x	x	
HR	x	x	x	x	x
BP	x	x	x	x	x
Weight	x	x	x	x	x
miRNA	x	x	x	x	x
Routine blood counts	x				x
Liver and renal function	x	x	x	x	
Cmax		x	x	x	
ADR		x	x	x	x
Genotype	x				

ADR = adverse drug reaction, BP = blood pressure, Cmax = maximum serum concentration, GAD7 = generalized anxiety disorder7, HAMA = Hamilton anxiety scale, HAMD = Hamilton depression scale, HR = heart rate, NRS = numerical rating scale, PHQ9 = patient health questionaires 9, PRS = pain relief scale, PSQI = Pittsburgh sleep quality index, QoL = quality of life, SF36 = short form 36.

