### 2.10. Outcomes measures

#### 2.10.1. Primary outcome.

The differential expression of miRNAs between CAPS groups and healthy control groups at baseline.The changes in abdominal pain scores before and after duloxetine treatment in patients with CAPS and their relationship with changes in miRNA.

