#### 2.12.2. Data analysis.

Statistical Package for the Social Sciences for Mac book air, version 26 will be used for data analysis. For descriptive statistics, we use proportions for categorical variables, mean ± SD for normal continuous data, median for non-normally continuous data. K-S tests will be used for the normality test. Descriptive statistic is used to describe the demographic characteristics and laboratory test results. Whole data of primary and secondary outcomes are repeated measure and continuous data. X2 test is used for comparison at different time points and intergroup differences in term of baseline data. If the difference is detected statistically significant, post hoc multiple pairwise comparison will be performed. The association of blood biomarkers, plasma concentration, genotype and clinical efficacy, medication adherence will be assessed by Spearman correlation analysis. *P* < 0.05 is considered statistically significant.

We use intention to treat and per protocol to deal with missing values, outlier values, lost follow-up and non-adherence respectively.

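### The baseline miRNA comparison sets patients and controls from different recruitment streams against each other with no adjustment for age or sex, so differences in either can appear as CAPS markers

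*Protocol article*

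**What the plan says.** All references are to the protocol article.

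- **Outcome.** Section 2.10.1 lists first among the primary outcomes "The differential expression of miRNAs between CAPS groups and healthy control groups at baseline". Section 2.3 says that this is meant to supply diagnostic biomarkers.
- **Source of patients.** Section 2.4: "We decide to recruit CAPS patients from the inpatient and outpatient of departments of gastroenterology".
- **Source of controls.** Section 2.4: "the healthy controls will be recruited from the individuals who visit the digestive endoscopy center for routine checkups of gastroscopy and colonoscopy".
- **Eligibility.** Section 2.5.1 gives the same age range to both groups: "All CAPS patients must meet all of the following criteria: age at 18 to 85; meet the Rome IV diagnostic criteria" for patients, "All healthy controls must meet all of the following criteria: age at 18 to 85; no abdominal pain and other gastrointestinal symptoms" for controls. Neither list contains a matching criterion.
- **Balance.** Section 2.12.1 sets 215 controls to 215 patients by a 1:1 ratio. This fixes numbers only.
- **Analysis.** Section 2.12.2 names an X2 test for comparisons over time and for "intergroup differences in term of baseline data", post hoc pairwise comparisons, and Spearman correlation. It names no regression and no covariate. Demographic characteristics are summarised descriptively.
- **Data available.** At visit 1, section 2.7 says: "Demographic and baseline data will be collected".

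**The concern.** In a non-randomised comparison, any factor that differs between the groups and also affects expression biases the contrast. Here the two groups reach the study by different routes: one through illness, the other through a routine check-up. Nothing in the stated design makes their age or sex distributions alike, and nothing in the stated analysis removes a difference if there is one.

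A miRNA that tracks age or sex but has nothing to do with CAPS can then be declared differentially expressed. Because the purpose is a diagnostic marker, such a finding would be carried forward as evidence about the disease. Testing whether the groups differ at baseline shows an imbalance at best; it does not correct the miRNA contrast.

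**Working it through.** **1. The plan's own figure.** 172 / (1 − 0.20) = 215 patients, and 1:1 gives 215 controls. This reproduces section 2.12.1. The 172 itself cannot be rebuilt, because no effect size is stated. If it is read as 172 per group in a two-sample comparison with two-sided α = 0.05 and power 0.95, it implies d = (1.960 + 1.645) × √(2/172) = 0.39.

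**2. Inputs that the article does not give (assumptions).**
- g, the age gap between the groups in SD units: 0.25 to 0.5. With an assumed age SD of 15 years this is 3.75 to 7.5 years.
- r, the correlation of a miRNA with age: 0.1 to 0.3.

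**3. Formula.** For a miRNA with no CAPS effect and unit SD, the spurious group difference is b = r × g. With n per group, the noncentrality is λ = b / √(2/n). The false-positive rate of an unadjusted two-sided 5% test is Φ(λ − 1.96) + Φ(−λ − 1.96). For n = 215, √(2/215) = 0.0964.

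| g (SD) | r | b | λ | False-positive rate |
|---|---|---|---|---|
| 0.25 | 0.1 | 0.025 | 0.26 | 5.8% |
| 0.25 | 0.2 | 0.050 | 0.52 | 8.1% |
| 0.25 | 0.3 | 0.075 | 0.78 | 12.2% |
| 0.5 | 0.1 | 0.050 | 0.52 | 8.1% |
| 0.5 | 0.2 | 0.100 | 1.04 | 17.9% |
| 0.5 | 0.3 | 0.150 | 1.56 | 34.3% |

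**4. Sex, by the same formula.** Assume a 20-point difference in the proportion female and a sex effect on expression of 0.2 to 0.5 SD. Then b = 0.20 × 0.2 = 0.04 to 0.20 × 0.5 = 0.10, and the rate is 7.0% to 17.9%.

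**5. Sample size does not help.** At g = 0.5 and r = 0.3 the rate is 28.5% with 172 per group and 34.3% with 215. The bias stays fixed while the standard error shrinks.

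**6. Effect of adjustment.** The setting was simulated with 4,000 runs, 215 per group, r = 0.3 and no CAPS effect. At g = 0.25 the unadjusted t-test rejects in 11.0% of runs and a linear model with age in 5.2%. At g = 0.5 the figures are 33.9% and 4.9%. Adjustment restores the nominal level.

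**The case against.** The strongest reply is that the article nowhere says that controls are unmatched or that the comparison is unadjusted. It is a condensed text, and a fuller protocol or analysis plan could add either. That is fair, and an unseen plan may already deal with the matter. But the article does set out how controls are selected, what ratio is used and which methods are applied. Followed as written, it leaves the confounding in place.

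Other objections also limit the point:

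- **The sentence on baseline differences is ambiguous.** A reader might infer that the plan tests balance and then compares miRNAs while ignoring the result. The article states no such sequence. Baseline miRNA is itself baseline data, so the X2 sentence may be the miRNA comparison. On either reading no covariate enters. Whether X2 suits continuous expression data is a separate matter.
- **A shared age range permits imbalance but does not create it.** The groups also share one hospital, one recruitment period and most exclusions. These narrow some differences but do not balance age or sex.
- **The size is wholly assumed.** At the low end (g = 0.25, r = 0.1) the rate is 5.8%, close to nominal.
- **The pilot's 11 miRNAs invite multiplication.** A reader might apply the rate to each of them. The article does not say that these 11 are the ones to be tested, and the inflation reaches only miRNAs that are associated with the unbalanced factor.

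**Conclusion.** The point holds as a possibility that the stated plan leaves open. The first primary outcome is a non-randomised contrast between two recruitment streams, the only stated balance is in number, and every named method is unadjusted. Age or sex differences can therefore appear as CAPS markers.

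Under the age assumptions above, the false-positive rate per affected null miRNA is about 6% to 34% instead of 5%. The documents cannot narrow that range. They also do not support the stronger conclusion that the groups will differ, or that an age or sex marker will be reported as a CAPS marker, because they give no age or sex distribution and no association of any miRNA with either factor. The change is still worth making, because the safeguard uses data already collected and costs almost nothing.

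**What to change.** In section 2.12.2, make the primary baseline comparison a linear regression of normalised (log) miRNA expression on group, adjusted for age and sex, both part of the demographic data taken at visit 1. Report the unadjusted comparison as secondary. State that significance tests of baseline balance are not relied on to deal with confounding.

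Two further steps might seem natural but are not recommended. Weight is recorded at every visit, but the disease may affect it, so adjusting for it could remove real signal. Matching only the controls still to be enrolled would change the selection rule in a study that the article describes as already under way.

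The cost is a little more analysis work and no new data. Intervals may widen slightly if the groups differ. For age, the standard error is multiplied by about √(1 + g²/4) × √(1 − r²). At g = 0.5 this is 1.031 × 0.995 = 1.026 for r = 0.1 and 1.031 × 0.954 = 0.983 for r = 0.3, that is, from about 3% wider to about 2% narrower.

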### 2.5. Eligibility criteria

#### 2.5.1. Inclusion criteria.

All CAPS patients must meet all of the following criteria: age at 18 to 85; meet the Rome IV diagnostic criteria; a signed and dated informed consent form; and commit to comply with study process and align with implementing the whole study process

All healthy controls must meet all of the following criteria: age at 18 to 85; no abdominal pain and other gastrointestinal symptoms; no organic lesions at gastroenterological endoscopy in latest 6 months; a signed and dated informed consent form; and commit to comply with study process and align with implementing the whole study process.

#### 2.5.2. Exclusion criteria.

Participants who meet either of the following criteria will be excluded: participants complicated with organic lesions; participants with contraindications to duloxetine; patients who are taking other antidepressant; participants with a history of intellectual disability, impaired consciousness, mental disorders, seizures; pregnant and lactating female; patients meet the diagnostic criteria for any psychiatric disorder and Statistical Manual of Mental Disorders criteria of depression or anxiety, diagnosed depression or anxiety; with Hamilton Anxiety Scale (HAMA) scores more than 14, Hamilton Depression Scale scores more than 18; with high blood pressure  > 140/90 mm Hg; with a history of recent abdominal surgery; with a history of ulcerative colitis, Crohn disease, celiac disease and a family history of colorectal cancer; with a history of angle-closure glaucoma, uncontrolled thyroid disease and tumor; patients who are unwilling or unable to comply with the study protocol or cannot to cooperate with follow-up; and participants who are considered unsuitable by the investigator to participate in this study.

### 2.6. Intervention

#### 2.6.1. Drugs.

The property of duloxetine (produced by LILLY DEL CARIBE, Inc) is white or off-white enteric-coated granules. 30 mg capsule: white opaque capsule body and blue capsule cap, 30 mg printed on the capsule; 60 mg capsule: white opaque capsule body and blue capsule cap, 60 mg printed on the capsule. Package: aluminum blister pack, 7 capsules per box, 14 capsules per box, 28 capsules per box.

Withdrawal of medications must be taper to complete withdrawal, and monitor the withdrawal response. If intolerance, return to the previously dose, and then reduction with lesser dose. Duloxetine should be swallowed, not chewed or crushed.

All drugs use was recorded by Hospital information system. All scales and scores were recorded and saved by computer, which were used to evaluate intervention.

#### 2.6.2. Intervention flow.

The intervention flow is illustrated in Figure 1.

**Figure 1. F1:**
[figure not shown]
Intervention flow. CAPS = centrally mediated abdominal pain syndrome, iw = once every 2 weeks, PRS = pain relief scale, qd = once per day, w = week.

### 2.7. Study procedure and timeline

The study procedure and timeline is illustrated as Figure 2 and Table 1. Heart rate, blood pressure, weight will be recorded at every visits. At the initial visit (visit1), patients will be diagnosed with CAPS by an experienced gastroenterologist. Patients and healthy controls will be screened by a experienced gastroenterologist. All of them will sign an informed consent form. Demographic and baseline data will be collected. The subjects will be asked to complete a series of questionnaires in order to get baseline scores. Baseline scores on the Numerical Rating Scale, the HAMA, Generalized Anxiety Disorder7, Hamilton Depression Scale, Patient Health Questionaires 9, Short Form 36, Pittsburgh sleep quality index will be obtained. Blood routine, biochemical indicators and genotype will also be carried out in the laboratory of Ruijin Hospital. On the ground of experimental method of Real-Time Fluorescence Quantitative PCR, the serum miRNAs will be sequenced between patients with CAPS and healthy control group.

**Table 1 T1:** Study timeline.

Visits	Screening period	Treatment period		Therapy termination	Follow-up period
	1	2	3	4	5 (Follow-up 1)
Treatment period (mo)	0	1	3	6	9
Informed consent form	x				
Demography and baseline	x				
Inclusion/exclusion	x				
NRS	x	x	x	x	x
HAMA/HAMD/PSQI/GAD7/PHQ9/SF36	x	x	x	x	x
PRS		x	x	x	x
QoL	x	x	x	x	x
Morisky questionnaire		x	x	x	
HR	x	x	x	x	x
BP	x	x	x	x	x
Weight	x	x	x	x	x
miRNA	x	x	x	x	x
Routine blood counts	x				x
Liver and renal function	x	x	x	x	
Cmax		x	x	x	
ADR		x	x	x	x
Genotype	x				

ADR = adverse drug reaction, BP = blood pressure, Cmax = maximum serum concentration, GAD7 = generalized anxiety disorder7, HAMA = Hamilton anxiety scale, HAMD = Hamilton depression scale, HR = heart rate, NRS = numerical rating scale, PHQ9 = patient health questionaires 9, PRS = pain relief scale, PSQI = Pittsburgh sleep quality index, QoL = quality of life, SF36 = short form 36.

**Figure 2. F2:**
[figure not shown]
Study procedure. ADR = adverse drug reaction, BP = blood pressure, Cmax = maximum serum concentration, GAD7 = Generalized Anxiety Disorder7, HAMA = Hamilton anxiety scale, HAMD = Hamilton depression scale, HR = heart rate, NRS = numerical rating scale, PHQ9 = patient health questionaires 9, PRS = pain relief scale, PSQI = Pittsburgh sleep quality index, QoL = quality of life, SF36 = short form 36.

After the initial visit, every patient starts to take duloxetine under the instruction of gastroenterologist. The initial dose is 30 mg qd. After 1 week, if tolerated, increase dose to 60 mg qd, or 30 mg qd continued. In the duration of therapy, altering dose of duloxetine based on pain relief scale (PRS) score. We suggest adding 30 mg every 2 weeks, however, the total dose should not exceed 120 mg qd.

During the treatment period, patients need to have 3 outpatient visits as follow-up including 1 month (visit 2), 3 month (visit 3) and 6 months (visit 4) after the treatmet, respectively. Patients will be required to complete the same questionnaires as at the initial visit and 2 additional questionnaires, including PRS and Morisky questionnaire. Biochemical indicators, Maximum serum concentration of duloxetine, blood miRNA will be tested in the laboratory of Ruijin Hospital. Adverse drug reaction will also be recorded.

After 24-week treatment period, there is a further 12-week outpatient post-treatment follow-up period. At the terminal visit (visit 5), patients will be required to complete all the rating scales except Morisky questionnaire. Adverse drug reaction will also be recorded. Micro RNA, genotype and blood routine will be tested again.

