### 2.8. Criteria for discontinuing the intervention

Sever adverse reactions; Any other disease which affects the efficacy of duloxetine, and determination of Adverse events; Patient is deemed unsuitable for continuing to take duloxetine by the researchers; Subjects withdraw informed consent form; Patients are reluctant to continue their treatment because of poor efficacy; and Lost to follow up.

The reasons for discontinuation and withdrawal would be recorded on the case report form. Subjects who signed informed consent but did not accept the intervention will be replaced. Subjects who signed informed consent, accept the intervention and subsequently withdraw will or may be not replaced.

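### The schedule records only adverse drug reactions, not all adverse events, in a study where every CAPS patient is treated, so the safety record may be incomplete

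*Protocol article*

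**What the plan says.** Section 2.7 of the protocol article names one clinical event item. After listing the assessments at visits 2 to 4 it states "Adverse drug reaction will also be recorded", and it repeats the sentence for visit 5, the last visit of the 12-week follow-up. Table 1 has an ADR row marked at visits 2, 3, 4 and 5, and its footnote expands the term: "ADR = adverse drug reaction, BP = blood pressure, Cmax = maximum serum concentration". No row covers adverse events irrespective of cause, and the article does not say who judges causality or how.

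On treatment, section 2.7 states that "every patient starts to take duloxetine under the instruction of gastroenterologist". The only comparison group is healthy controls, who according to the Abstract give blood at the initial visit.

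Other safety-relevant data are collected without any causality judgement. The text of 2.7 says "Heart rate, blood pressure, weight will be recorded at every visits". Table 1 has a row for "Liver and renal function" at visits 1 to 4, and schedules the pain rating and the mood, sleep and quality-of-life scales at all five visits.

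Section 2.8 lists among its discontinuation criteria "Sever adverse reactions" and, as the next item, "Any other disease which affects the efficacy of duloxetine, and determination of Adverse events". It adds: "The reasons for discontinuation and withdrawal would be recorded on the case report form".

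**The concern.** An adverse event is any untoward occurrence during the study. An adverse drug reaction is one that has been attributed to the drug. If the form asks only for the second, causality becomes a condition for entering the record when it should be a field within it. An event judged unrelated on the day leaves no entry, so nobody can revisit that judgement at analysis.

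This design is poorly placed to absorb such a filter. With an untreated CAPS group, an excess of some symptom could show in the comparison of groups even if individual judgements were wrong. Here all patients are treated and the comparators are healthy people, so attribution case by case is the only route by which a clinical event is linked to duloxetine. The disease is itself abdominal pain, so a drug-related abdominal symptom can easily be read as CAPS.

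At stake is the completeness of the tolerability information for a drug given and titrated in all 215 patients.

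**Working it through.** No figure in the plan bears on this point, so the check is mainly a comparison of passages.

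**1. What is scheduled as a clinical event.** Section 2.7, treatment visits: adverse drug reaction. Section 2.7, visit 5: adverse drug reaction. Table 1, visits 2 to 5: ADR. The footnote to Table 1 and the legend of Figure 2 both expand ADR the same way. The wording is consistent, and nothing in the article widens it to events of any cause.

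**2. What is collected whatever the cause.**
- Pain rating (NRS): visits 1 to 5.
- HAMA, HAMD, PSQI, GAD7, PHQ9, SF36: visits 1 to 5.
- Heart rate, blood pressure, weight: visits 1 to 5.
- Liver and renal function: visits 1 to 4.
- Routine blood counts: visits 1 and 5.
- Reasons for discontinuation and withdrawal: case report form (section 2.8).

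Harm that shows in any of these would leave a trace. A clinical symptom outside them, such as nausea, would not unless it was attributed to the drug or led to discontinuation. Drug-related abdominal pain would raise the NRS, but there it would read as poor response, not as harm.

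**3. Whether groups could be compared instead.** Treated CAPS patients: all. Untreated CAPS patients: none. Healthy controls: no symptoms at entry and no disease. No event rate in untreated CAPS patients is available from within the study.

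**4. Section 2.8 against section 2.7.** The criterion that harm triggers uses the term adverse reactions, which matches the ADR row. The item after it has another disease as its subject. Its most natural reading is an intercurrent illness that interferes with judging efficacy and adverse events. The sentence can be read in more than one way, and section 2.8 uses both terms without saying how they relate.

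**5. Size, on assumed rates only.** The documents give neither an event rate nor an attribution rate. Let p be the proportion of the 215 patients with a drug-caused event and s the share of those events attributed to the drug. With no false attribution, the number recorded is 215 × p × s.
- p = 5%, s = 50%: 215 × 0.05 × 0.5 = 5.4 recorded of 10.75.
- p = 5%, s = 90%: 215 × 0.05 × 0.9 = 9.7 of 10.75.
- p = 20%, s = 50%: 215 × 0.20 × 0.5 = 21.5 of 43.
- p = 20%, s = 90%: 215 × 0.20 × 0.9 = 38.7 of 43.

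The range, about 5 to 39 recorded, is set wholly by the assumptions. The formula also leaves out background symptoms wrongly blamed on duloxetine. In the third case, false attribution in 43 − 21.5 = 21.5 patients would bring the count back to 43, and more than that would push it above. The direction of the error is therefore not fixed either.

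**The case against.** The strongest case on the other side is that this is a matter of terminology. The article never says that unrelated events go unrecorded. ADR may be loose wording for adverse event, and definitions, causality procedure and form content are commonly left to a full protocol and case report form that are not shown. The declared outcomes in section 2.10 contain no safety endpoint, and section 2.12.2 promises no tolerability estimate. Much is collected without attribution, including pain at every visit.

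Most of this stands as a limit on the claim. It does not remove it. The article is not silent on the item: it names it in the text and in the schedule, each time with the term that presupposes attribution. Staff who follow that text would record less than they should. If ADR was meant broadly, the same change serves as a clarification.

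Three stronger readings are tempting and are not supported.
- A reader might infer that the adverse-event wording in section 2.8 is a stopping criterion with no scheduled data behind it. The item is most naturally triggered by another disease, and the criterion that harm does trigger matches the scheduled ADR row.
- A reader might infer that drug harm mistaken for CAPS is lost. Part of it would still appear in the scales, vital signs, laboratory tests and discontinuation reasons.
- A reader might infer that reported tolerability will look too favourable. Misattribution can run both ways when every patient knowingly takes the drug, and the documents do not show which way dominates.

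**Conclusion.** The point holds in a limited form. Section 2.7 and Table 1 schedule only adverse drug reactions at visits 2 to 5, and no untreated CAPS group exists from which a wrong attribution could be recovered. Followed as written, clinical symptoms judged unrelated, including those that resemble CAPS, have no scheduled place beyond the attribution-free data listed above. The safety record may be incomplete, and the attributions could not be re-examined afterwards. This rests on taking the term ADR at its stated meaning.

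Size and direction cannot be computed from the documents; the figures above are illustrations on assumed rates and carry no weight in the conclusion. The miRNA, pain, mood, sleep and quality-of-life outcomes are not affected. The change is worth making because a filter at data entry cannot be undone at analysis.

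**What to change.** In section 2.7 and in the ADR row of Table 1, replace the item with all adverse events, recorded at the same visits with onset, severity and the investigator's causality judgement as a separate field. Report all adverse events, with adverse drug reactions as the subset judged related.

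In section 2.8, use the same terms as in 2.7 and reword the item about another disease so that its trigger is clear. The clinical content of that criterion is for the investigators to decide; the need here is only that the two sections agree.

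The cost is a change of wording in the schedule and case report form, and slightly more recording at existing visits. No extra visit or procedure is needed.
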